### Confidentiality {27}

Personal data of potential and enrolled participants (name, e-mail address, and phone number) will only be collected so that participants can be contacted throughout the trial (e.g., receive the links to the different assessments). Personal data of parents (name and e-mail address of both parents/other legal guardians) will only be collected for underaged participants in order to obtain parental informed consent in accordance with German law. Personal data will be collected via the software REDCap, which is running on encrypted, secure faculty servers of the LMU Munich and will—at no point—be saved outside of the REDCap system. Only the study team (the first author of this paper and master students involved in data collection and in case of adverse events licensed clinical psychologists within team) will have access to the personal data as they need it to manage and monitor data collection or to react to adverse events. Everyone with access to the personal data has to sign an agreement stating that personal data must not be used for any other purpose than managing and monitoring data collection. For all further purposes (including logging into the m-Path app), participants will receive a pseudonym. After data collection for this study is finished, all personal data will be deleted so that the final dataset is completely anonymized. Potential participants will be informed in detail about data management and data protection in this trial before they take informed consent. The data protection and management procedures have been approved by the data protection officer of LMU Munich.

### Plans for collection, laboratory evaluation, and storage of biological specimens for genetic or molecular analysis in this trial/future use {33}

n/a, explanation: No biological specimens will be collected as part of this study.

## Statistical methods

### Statistical methods for primary and secondary outcomes {20a}

#### Primary analyses

A linear mixed-effects model will be computed to analyze whether the two versions of the app reduced depressive symptoms (sum score on the IDS, primary outcome variable) relative to the control condition. In the model, the effect of condition (full RNT-focused intervention, concreteness training intervention, waiting list control condition), time (pre-intervention, post-intervention), and condition × time interaction will be tested. Simple slope tests will be conducted to determine whether (a) the full RNT-focused intervention significantly reduced depressive symptoms relative two the waiting list control condition and (b) the concreteness training intervention significantly reduced depressive symptoms compared to the waiting list control condition.

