### Outcomes {12}

Outcomes will be assessed at three measurement timepoints: pre-intervention (i.e., pre-randomization), post-intervention (6 weeks after pre-intervention), and follow-up (18 weeks after pre-intervention).

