### Sample size {14}

We conducted a power analysis in G*Power [60] based on the minimal clinically important difference (MICD) in depressive symptoms (primary outcome). Measures of depressive symptoms have an established MCID of *d* = 0.48 [61], which also provided the basis for the power analysis in other recent trials testing app-based prevention [54]. Using this effect size, with 90% power and an alpha level of 0.05, the sample size required for a 2-arm two-sided comparison at post-intervention would be 93 participants per arm. To account for 20% expected dropout at post-intervention, a total sample size of 351 (117 per trial arm) will be needed to test whether the two app-based interventions (the full RNT-focused intervention and the concreteness training intervention) significantly reduce depressive symptoms relative to the waiting list control condition. The required sample size was calculated for a two-arm comparison (even though the study has three arms) as we do not have any a priori hypotheses regarding whether one of the apps will be more efficacious.

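### The primary model leaves each arm its own pre-randomization IDS mean: the contrast is unbiased but less precise than baseline adjustment, and the stated 90% power was computed for a different comparison

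*Protocol article*

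**What the plan says.** Three sections of the protocol article bear on this.

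- **Primary analyses {20a}.** A linear mixed model for the IDS sum score tests "the effect of condition (full RNT-focused intervention, concreteness training intervention, waiting list control condition), time (pre-intervention, post-intervention"), together with their interaction. Simple slope tests then compare each app with the waiting list. No baseline covariate and no common-baseline constraint is named. Secondary analyses repeat this model for RRS, PSWQ, PTQ, GADQ-IV and SPIN.
- **Sample size {14}.** The basis is "Measures of depressive symptoms have an established MCID of *d* = 0.48 [61]". The target is 90% power at alpha 0.05, and the stated result is that "the sample size required for a 2-arm two-sided comparison at post-intervention would be 93 participants per arm". Allowing for 20% dropout, "a total sample size of 351 (117 per trial arm) will be needed". No pre-post correlation is stated.
- **Outcomes {12}.** The first assessment is "pre-intervention (i.e., pre-randomization"), and the primary outcome is the IDS sum score at post-intervention.

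The section on missing data {20c} adds FIML and intention-to-treat.

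**The concern.** Because baseline is measured before allocation, the three arms share one true baseline mean by design. A model with a condition main effect and time coded pre/post estimates three separate baseline means and so discards that knowledge. The condition × time term then subtracts the whole observed baseline difference instead of the fraction that the pre-post regression supports, so chance imbalance is over-corrected whenever that regression slope is below 1.

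Two things are at stake. The first is precision, on the primary outcome and on the five secondary outcomes that use the same model. The second is the link between sample size and analysis: the trial is sized for a difference in post-intervention scores, the primary outcome is defined as a post-intervention score, but the planned test is on change. The 90% therefore does not describe the planned test unless a pre-post correlation is supplied.

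**Working it through.** **Inputs from the protocol.** d = 0.48, two-sided alpha 0.05, power 90%, 93 evaluable and 117 randomized per arm, 20% dropout (Sample size {14}). **Assumed, because not given:** the pre-post correlation r of the IDS, shown over a range; d standardized on the post score; pre and post SDs equal unless stated.

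**1. The protocol's own figure.** For a two-sample t-test on post scores (noncentral t), power is 0.8994 at 92 per arm and 0.9025 at 93. Then 93/0.8 = 116.25, rounded up to 117, and 3 × 117 = 351. All three figures reproduce, for a post-only comparison.

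**2. What the planned contrast is.** With complete data, the interaction contrast is the difference in mean change. Fitting the model to simulated complete data confirmed this: estimate and standard error matched the raw change-score contrast (−0.428, SE 0.171 at r = 0.3; −0.539, SE 0.155 at r = 0.5).

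**3. Variance relative to a post-only contrast (equal SDs).** Change: 2(1−r). Baseline-adjusted: 1−r². The ratio of adjusted to change is (1−r²)/[2(1−r)] = (1+r)/2, below 1 for every r < 1.

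**4. Power at 93 per arm**, using standardized effect 0.48/√variance:

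| r (assumed) | change variance | adjusted variance | power, change | power, adjusted |
|---|---|---|---|---|
| 0 | 2.00 | 1.00 | 63% | 90% |
| 0.3 | 1.40 | 0.91 | 79% | 93% |
| 0.4 | 1.20 | 0.84 | 84% | 94% |
| 0.5 | 1.00 | 0.75 | 90% | 96% |
| 0.6 | 0.80 | 0.64 | 95% | 98% |
| 0.7 | 0.60 | 0.51 | 99% | 99.5% |

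The change contrast reaches 90% at r = 0.496. The adjusted contrast is never below 90%, because 1−r² cannot exceed 1.

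**5. Effect of FIML with dropout.** With 117 baseline scores and 117 × 0.8 = 93.6 post scores per arm, and separate baseline means, the per-arm variance is (1−r²)/93.6 + (1−r)²/117. Power is then 82% at r = 0.3, 87% at 0.4 and 92% at 0.5. It crosses 90% at r of about 0.46.

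**6. Restricted baseline spread.** Entry requires PHQ-9 of 9 or less, which plausibly narrows the pre-intervention IDS. With pre SD = s and post SD = 1, the change variance is s² + 1 − 2rs, while the adjusted variance stays 1−r². An illustrative simulation of the PHQ-9 cut, assuming an unrestricted r of 0.6 to 0.7, gives r of 0.51 to 0.65 and s of about 0.85 to 0.93. At the corners:

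| s | r | change variance | adjusted variance | reduction | power, change | power, adjusted |
|---|---|---|---|---|---|---|
| 0.85 | 0.51 | 0.856 | 0.740 | 14% | 94% | 97% |
| 0.93 | 0.51 | 0.916 | 0.740 | 19% | 92.5% | 97% |
| 0.85 | 0.65 | 0.618 | 0.578 | 6% | 98.6% | 99% |
| 0.93 | 0.65 | 0.656 | 0.578 | 12% | 98.0% | 99% |

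The change contrast matches the post-only variance at r = s/2, that is 0.425 for s = 0.85 and 0.465 for s = 0.93. In general, change and adjustment tie only if the post-on-pre slope is exactly 1.

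**The case against.** The planned analysis is valid. Randomization makes the interaction contrast unbiased, a condition × time mixed model is in common use, and sizing by a post-score t-test is a frequent simplification. All of that stands, so this is a matter of efficiency and of what the power statement refers to.

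A reader might infer from the r = 0.3 and 0.4 rows that the trial is underpowered. The protocol does not support that. It states no correlation, FIML lowers the 90% threshold to about 0.46, and a narrower baseline SD lowers it too. Under the illustrative restricted values above, the planned test stays above 90%. A reader might likewise take 25% as the variance saving; that needs equal SDs and r = 0.5, and under the restricted values the saving is about 6 to 19%.

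It can also be said that the SAP, which the protocol promises separately, may add a baseline covariate or constraint. This helps only in part: covariance structure and covariates can properly wait for the SAP, but the protocol already names a condition effect and pre-intervention as a level of time. That is a stated choice, not a silence.

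**Conclusion.** The point holds as a free improvement together with a mismatch in the power basis; a power shortfall is not shown. Two parts need no value of r: the planned contrast is never more precise than a baseline-adjusted one, and 93 per arm with 90% power belongs to a post-only comparison. The size does depend on assumptions. With equal SDs the adjusted variance is (1+r)/2 of the change variance; with a narrower baseline SD (0.85 to 0.93 of post) and r of 0.51 to 0.65, adjustment saves about 6 to 19%. With equal SDs the planned contrast has 90% power only from r of about 0.46 (FIML, 20% dropout) to 0.50 (complete data) upward. Baseline adjustment keeps at least 90% whatever r is.

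**What to change.** In the primary analyses section, specify a constrained-baseline mixed model: one common pre-intervention mean (no condition main effect), time, condition × time, unstructured covariance, FIML retained. Alternatively, analyse week-6 IDS adjusted for baseline IDS. The two are not identical when post scores are missing, because complete-case ANCOVA drops the baseline scores of those who left, whereas the constrained model keeps them; the text should say which is meant. Use the same form for the five secondary outcomes.

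In the sample size section, state that 93 per arm comes from a post-intervention-only comparison and is conservative for the baseline-adjusted model. If the present model is kept instead, state the assumed pre-post correlation and the power that follows from it.

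The cost is wording only. Baseline IDS is already collected and the sample size of 351 does not change.

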#### Secondary analyses

The primary analyses will be repeated for the secondary outcomes depressive rumination (RRS sum score), worry (PSWQ sum score) content-independent RNT (PTQ sum score), generalized anxiety symptoms (GADQ-IV sum score), and social anxiety symptoms (SPIN sum score), respectively. *P-*values will be adjusted using Holm’s procedure [74] to reduce the chance of finding false positives due to multiple outcome variables.

#### Exploratory analyses

Comparison of the two active conditions: As described in the section objectives {7}, we do not have any a priori predictions about the superiority of one of the two app-based interventions over the other intervention. To explore potential differences in the outcome variables at post-intervention between the two active conditions, we plan to conduct a Bayesian analysis. In contrast to frequentist analyses, in which the absence of a significant effect cannot be considered as proof for the null hypothesis, in Bayesian analyses, the strength of evidence for two competing hypotheses can be assessed [75, 76]. Hence, this approach is suitable to objectively explore potential differences between experimental conditions when there are no a priori hypotheses as it also allows to express with how much certainty there are no differences between the conditions.

Effects at follow-up: All analyses will be adapted to test whether the predicted effects and potential differences between the two active conditions extend to the follow-up timepoint.

Effects on diagnoses: Logistic regression analyses will be conducted to explore whether the app-based interventions decrease the probability of fulfilling the criteria (as indexed by standard cut-offs on self-report questionnaires) for a depressive episode, generalized anxiety disorder, and social anxiety disorder at post-intervention and/or follow-up.

### Interim analyses {21b}

A full, detailed statistical analysis plan (SAP), including plans for any interim analysis, subgroup analysis, and sensitivity analysis of the primary outcomes, will be prepared and finalized before the analysis. The SAP will be made available over the platform where the study was registered (German Clinical Trials Register https://www.drks.de, study ID: DRKS00027384) before the end of recruitment.

### Methods for additional analyses (e.g., subgroup analyses) {20b}

Methods for additional analyses will also be included in the detailed analysis plan that will be finalized before the analysis.

### Methods in analysis to handle protocol non-adherence and any statistical methods to handle missing data {20c}

Missing data will be inspected and handled via full information maximum likelihood (FIML). The analyses will be intention-to-treat (ITT) [77] analyses.

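### FIML recovers no missing outcomes in the exploratory diagnosis regressions, so as written they become complete-case analyses despite the intention-to-treat statement

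*Protocol article*

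**What the plan says.** The protocol article handles missing data in one short section, {20c}. It states "Missing data will be inspected and handled via full information maximum likelihood (FIML") and "The analyses will be intention-to-treat (ITT) [77] analyses". No analysis is exempted from either sentence.

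The analyses it covers are of two kinds:

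- **Primary and secondary outcomes.** Under Primary analyses, "A linear mixed-effects model will be computed to analyze whether the two versions of the app reduced depressive symptoms". Its terms are condition, "time (pre-intervention, post-intervention), and condition × time interaction will be tested". The same model is repeated for the secondary scales.
- **Diagnoses.** Under Exploratory analyses, "Logistic regression analyses will be conducted to explore whether the app-based interventions decrease the probability of fulfilling the criteria", for depression, generalized anxiety disorder and "social anxiety disorder at post-intervention and/or follow-up". Covariates are not named. The text does not say whether each timepoint is modelled separately, although that is the natural reading.

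Three other sections bear on the point. Eligibility criteria {10} excludes anyone above the cut-off on the PHQ-9, GAD-7 or SIAS at entry. Sample size {14} expects 20% dropout at post-intervention. Objectives {7} says that lower symptom and RNT scores do not test prevention directly, and assigns the exploration of prevention to the cut-off analyses.

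**The concern.** FIML uses partly observed participants through the likelihood. In the mixed model for IDS this works: a participant who leaves before week 6 still has a baseline IDS in the outcome vector, and that score informs the expected week-6 value. A logistic regression of one later binary outcome has no such second observation. The participant either has the outcome or adds nothing.

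The protocol therefore names a method that fits its continuous outcomes and extends it, unchanged, to analyses where it has no effect. A reader of the eventual report would take the diagnosis results as intention-to-treat results with missing data handled, when they would be results in completers. In an unblinded trial where only the app arms have tasks to do, completers need not be comparable across arms. In a prevention trial, the diagnosis results are also the ones most likely to be read as evidence of prevention.

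**Working it through.** **Inputs**

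- Sample size {14}: d = 0.48, 90% power, two-sided alpha 0.05, 93 evaluable per arm, 20% dropout at post-intervention, 117 per arm, 351 in total.
- Eligibility criteria {10}: scores above 9 on the PHQ-9, above 9 on the GAD-7 or above 35 on the SIAS exclude.
- Secondary outcomes, under Outcomes {12}: PHQ-9, GAD-7 and SIAS are taken at all three timepoints.

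**1. The plan's own figure.** The noncentral-t calculation gives 93 per arm (power 0.9025). Then 93 / 0.8 = 116.25, rounded up to 117, and 3 × 117 = 351. The stated figures reproduce. Expected completers are 117 × 0.8 = 93.6 per arm, so the planned power for the primary comparison does not depend on recovering missing data.

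**2. What FIML does in the logistic model.** Let p be the modelled probability of a diagnosis given a participant's covariates.

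- Outcome observed: the contribution is p if positive, 1 − p if negative.
- Outcome missing: sum over both possible values, p + (1 − p) = 1, so the log-likelihood contribution is 0.

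This holds whatever fully observed baseline covariates are in the model. A baseline score makes the missing-at-random assumption more plausible, but it does not bring the participant back. Baseline diagnosis cannot serve as an earlier wave either, because it is negative for everyone enrolled.

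A numerical check used two arms of 117, 20% of outcomes missing, and assumed diagnosis probabilities of 0.22 and 0.12:

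| Fit | Intercept | Condition coefficient |
|---|---|---|
| FIML, missing outcomes summed out | −1.4534 | −0.1047 |
| Complete cases | −1.4534 | −0.1047 |

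**3. How many are left out.** At post-intervention: 117 × 0.2 = 23.4 per arm and 351 × 0.2 = 70.2 overall. The protocol gives no dropout figure for week 18.

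**4. What that could do.** With 20% missing in each arm, let p₁ and p₀ now be the diagnosis rates among completers in an app arm and the control arm, and q₁ and q₀ the unknown rates among dropouts. The rate in all randomised participants of an arm is 0.8p + 0.2q. The completer difference therefore departs from the full difference by 0.2 × [(p₁ − q₁) − (p₀ − q₀)]. Each 10 percentage points by which the completer–dropout gap differs between arms moves the risk difference by 0.2 × 10 = 2 points. The documents give nothing from which to fix the size or sign of that gap.

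**5. The primary model, for comparison.** Large-sample simulation, 400,000 per arm, true effect −0.48 SD, 20% dropout per arm. The correlations and dropout slopes are assumptions (baseline–post 0.5–0.6, auxiliary–post 0.4–0.6, auxiliary–baseline 0.3–0.5).

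| Dropout driven by | Two-wave likelihood estimate |
|---|---|
| Baseline IDS, same or different slope by arm | −0.48 |
| An omitted baseline variable, same slope in both arms | −0.48 |
| An omitted baseline variable, different slopes by arm | −0.50 to −0.59 (about −0.48 once the variable is added) |

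The two-wave model goes wrong only in the last case.

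**The case against.** Four things can be said for the protocol.

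- **The regressions are exploratory** and use self-report cut-offs. That is correct, and no confirmatory conclusion depends on them.
- **The text does not fix a single-timepoint model.** Also correct. A repeated-measures logistic model over weeks 6 and 18 would use some participants who miss one wave. Someone who leaves before week 6 and does not return would still contribute nothing. Section {18b} ties reimbursement to completing all three assessments, so a participant who misses week 6 has lost that reason to return.
- **Complete-case logistic regression is the maximum-likelihood fit**, and it is valid if missingness depends only on the modelled covariates. True, so the FIML sentence is not false here; it is empty. The intention-to-treat sentence is what is not met in substance.
- **Detail may be in the SAP.** Sections {21b} and {20b} promise one, with sensitivity analyses of the primary outcomes. But the protocol does not leave this matter open. It states a method for all analyses, and for this class the method does not do the work.

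A reader might also infer something stronger: that the primary model mishandles dropout because it has two waves and no auxiliary variables, and that the resulting bias favours the apps. The documents do not support that. A two-wave likelihood model is a standard analysis. Auxiliary variables are not excluded anywhere, and they are commonly left to a SAP. The direction is not known either. With no true effect and an assumed 30% app and 10% control dropout, the bias is −0.05 to −0.12 SD if high-RNT app users leave, which is 10–25% of 0.48. It is +0.09 to +0.10 SD if low-RNT app users leave. Neither pattern is in the protocol.

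**Conclusion.** The point holds for the diagnosis analyses only. On the natural single-timepoint reading, FIML reduces exactly to complete cases, and about 20% of randomised participants (some 70 of 351) drop out of the post-intervention regressions, contrary to the intention-to-treat statement. That number rests on the protocol's own dropout expectation. The effect on the estimated differences cannot be sized from the document.

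The consequence is limited: the analyses are exploratory, and neither the primary comparison nor the sample size changes. It still deserves correction, because these are the analyses through which the protocol means to explore prevention.

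The primary model stands. It is valid if week-6 dropout depends only on condition and baseline IDS. Dropout related to RNT differently by arm would bias it, but whether that will happen, how strongly and in which direction is unknown.

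**What to change.** In {20c}, restrict FIML to the mixed models and state a separate method for the diagnosis analyses:

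1. Multiply impute the continuous PHQ-9, GAD-7 and SIAS scores within arm, using the baseline and other-wave scores already collected.
2. Apply the cut-offs to the imputed scores.
3. Fit the logistic regression adjusted for the baseline score of the same scale, and pool over imputations.

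Imputing the scores rather than the diagnosis lets the baseline information be used, since baseline diagnosis is the same for everyone. The method still assumes that data are missing at random given the variables in the imputation model.

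The cost is a little more analysis work and a few sentences of text. No new data are needed and the sample size is unchanged. If week-18 scores are used to impute week 6, the week-6 diagnosis results must wait until follow-up ends.

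Optionally, add a sensitivity analysis of the primary outcome with baseline RNT or the week-18 wave in the model, as a check against arm-specific dropout related to RNT. The primary model itself need not change.
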